### Method of Randomization and Allocation Concealment

Multi-stage cluster sampling was done among publicly funded schools in Madrid. In a first stage, we selected all schools fulfilling the abovementioned inclusion criteria. In a second stage, these centers were randomized 1:1 to the intervention and control groups. Ten schools (5 primary schools and 5 secondary schools) were offered participation in each arm of the trial, with a list of back-up schools in case of refusal to participate (2 primary schools and 7 secondary schools). This process would enable participation of about 96 classrooms in each cluster, including about 4,500 students overall (mean number of students per classroom is 23 in primary schools and 25 in secondary schools). Due to the study design, allocation could not be concealed, and the study was not blinded to participating schools or researchers. Psychological and bullying assessments were based on student reports (self-report or peer-report) on an online platform, with students unaware of the study hypotheses and no direct assessments of the outcome measures by members of the research group.

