#### Concomitant Intervention and Adherence to Intervention Guidance

The following information is collected through questionnaires specifically designed for the study: additional anti-bullying policies and activities available at all the participating schools, as well as program completion (e.g., proportion of teachers and parents completing the training online, number of classrooms participating in the intervention at each school, number of hours of the educational program completed by each participating classroom) and adherence to intervention recommendations (i.e., adherence to recommendations included in the personalized plans) in the intervention group schools. Students and teachers were asked online how many sessions of the educational program they had completed. Likewise, during the visit to schools after implementation of the intervention program, the researchers collected information on the number of sessions that the teachers had completed in each class group and contrasted this information with that provided by the school management team. As for families, the teaching units had a specific access link for each educational center to record the number of users who accessed each session and the time spent on the training. Based on these data, an adherence score will be calculated for each experimental school.

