#### Planned Analyses

Demographic, educational, and bullying variables will be compared between the intervention and control groups at baseline using parametric tests, as appropriate. Multi-level mixed model analyses (three levels: school, classroom, and student) will be performed to assess the effect of treatment group (intervention vs. control group) on each outcome variable, while controlling for school socio-economic status, primary vs. secondary school, sex, and age. Additional sensitivity analyses will be performed in the group of students with SEN, where we expect to detect a similar direction of the effects, but with a larger magnitude. In the intervention group, additional analyses will test the potential effect of covariates on the effect size of the intervention, including intensity of the intervention, concomitant activities, primary vs. secondary school, bullying rates at baseline, rural vs. urban environment, and proportion of students with SEN, among others.

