### Trial Status

The feasibility study was conducted between March and May 2018. Selection, randomization, and recruitment of schools started in November 2018 and were completed in January 2019. Baseline assessment of the 20 participating schools (10 in each arm) started in late January 2019 and was completed in early February. In the intervention group, the 12-week intervention program was implemented from February through early May 2019. The post-intervention assessment was performed between late May 2019 and early June 2019. The one-year follow-up assessment will take place during the school year 2020-2021.

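### Effect modification is to be tested inside the intervention arm alone, which contains no contrast with control to be modified

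*Protocol article*

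**What the plan says.** Planned Analyses, in the protocol article, sets out a three-level mixed model (school, classroom, student) "to assess the effect of treatment group (intervention vs. control group) on each outcome variable". There the effect is a comparison between arms.

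The same paragraph later turns to moderators: "In the intervention group, additional analyses will test the potential effect of covariates on the effect size of the intervention". The covariates are given as "including intensity of the intervention, concomitant activities, primary vs. secondary school, bullying rates at baseline, rural vs. urban environment, and proportion of students with SEN", and the list is left open. No treatment-by-covariate interaction that uses the control arm is stated.

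Students with SEN have an analysis of their own: "Additional sensitivity analyses will be performed in the group of students with SEN". It is not restricted to one arm.

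On intensity, the section on concomitant intervention and adherence says: "Based on these data, an adherence score will be calculated for each experimental school".

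**The concern.** To modify an effect is to change the difference between intervention and control. The plan names that target but restricts the data to one arm, where the difference cannot be estimated. What can be estimated there is whether some intervention schools ended lower, or fell further, than others. Schools differ in this way without any program: primary and secondary schools may follow different courses over a school year, and a school with an unusually high measured rate tends to measure lower next time.

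At stake is how the moderator results are read. A difference between types of school that would also have appeared under conventional practices could be presented as the program working better in one type than another.

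**Working it through.** **1. What each analysis estimates.** The plan gives no figure to reproduce here, so the check starts from the estimand. Let b be the natural association of a covariate with the outcome (or its change), and d the true modification of the effect.

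- Slope in the intervention arm: b + d
- Slope in the control arm: b
- Two-arm interaction: (b + d) - b = d

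The within-arm slope equals d only if b = 0, and one arm cannot show whether b = 0.

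**2. Which covariates exist in both arms.**

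| Covariate | Both arms? | Where stated |
|---|---|---|
| School type | Yes | Randomization section: "Ten schools (5 primary schools and 5 secondary schools) were offered participation in each arm of the trial" |
| Baseline bullying rate | Yes | Study Procedures: both groups assessed at baseline |
| Rural or urban | Yes | A feature of the school's location |
| Proportion with SEN | Yes | Section on students with SEN: numbers collected at each school |
| Concomitant activities | Yes | Section on concomitant intervention: all participating schools |
| Intensity or adherence | No | Same section: experimental schools only |

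**3. Baseline bullying rate with no treatment effect (d = 0).** Inputs: prevalence 3.8% and about 4,200 pupils in 20 schools, so 4,200/20 = 210 per school (Sample Size Calculation). The between-school SD is not given, so a range is assumed. True school rates are taken as unchanged between assessments.

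Sampling variance of a school rate = 0.038 × 0.962 / 210 = 0.00017408, or 1.741 squared percentage points (SD 1.32 points).

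Slope of change on baseline = -1.741 / (1.741 + SD²). Slope of endpoint on baseline = 1 + that value.

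| Assumed between-school SD (points) | Change on baseline | Endpoint on baseline |
|---|---|---|
| 0.5 | -1.741/1.991 = -0.874 | +0.126 |
| 1.0 | -1.741/2.741 = -0.635 | +0.365 |
| 1.5 | -1.741/3.991 = -0.436 | +0.564 |
| 2.0 | -1.741/5.741 = -0.303 | +0.697 |

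The sign depends on a modelling choice that the article does not state. The true modification is zero in every row.

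**4. How often a within-arm test would mislead.** Simulation with no effect and no modification: 10 schools per arm, 225 pupils per school (4,500/20, from the randomization section), 3,000 runs per scenario, two-sided 5% level, change in school rate as outcome.

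- *Baseline rate.* Assumed prevalence 3.8%, 5% or 8%; between-school SD 0.2, 0.4 or 0.6 on the log-odds scale; correlation of true school levels over time 1.0 or 0.8. The within-arm test rejects in 15% to 54% of trials (29% to 38% at 3.8% prevalence and SD 0.4). The two-arm interaction has a mean slope near zero (-0.013 to +0.018) and rejects in 4.7% to 9.6%.
- *School type, natural change in both arms* (log-odds SD 0.3). If primary schools fall from 7% to 4.2% while secondary schools stay at 5%, the within-arm test flags school type in 44% of trials and the interaction in 5.5%. If primary schools alone fall by 30% from 5%, the figures are 17% and 4.6%. With no natural difference, both are near 5%.

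**5. Precision of the valid analysis.** Take school summaries with equal variance s² and 5 primary and 5 secondary schools per arm. The main effect has variance 2s²/10 = 0.2s²; the interaction with school type has variance 4s²/5 = 0.8s². The interaction's standard error is √(0.8/0.2) = 2 times that of the main effect.

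**The case against.** The strongest reply is that the article leaves the model open. It specifies no change score, and model form is commonly left to the full protocol or SAP. This stands against one tempting inference: that the plan is bound to show the program working better where bullying is more common. That sign needs change regressed on baseline; with the endpoint rate as outcome it reverses. Even under a change score, the false signal appears in a minority of null trials in most of the scenarios examined. The reply does not rescue the analysis, because what the article does fix, the analysis set and the target, are incompatible under either model.

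Three other readings also go further than the text:

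- Regression to the mean does not explain all the moderators. It concerns the baseline rate; for the others the issue is prognosis or natural change, and without such differences the within-arm test of school type holds its level.
- A reader might count six covariates against 10 schools and infer that almost no degrees of freedom remain. The article does not say that the covariates enter one model together or that all are measured at school level.
- A reader might infer from the school adherence score that classroom session data are discarded. The article defines the score but does not say that it is the only measure of intensity to be used.

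It is also fair to say that intensity can be studied only within the intervention arm, and that these are additional analyses, listed last.

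**Conclusion.** The point holds for the five covariates available in both arms: restricted to the intervention group, the planned analysis cannot answer the question it is given. This is a stated choice, not a detail left out of a condensed article.

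Its size depends on assumptions that the documents do not supply, namely the between-school SD, the stability of school rates over time and the outcome form. With no true effect, the spurious slope on baseline rate runs from about -0.87 to -0.30 for change and from about +0.13 to +0.70 for the endpoint. For school type, the size depends entirely on how differently primary and secondary schools would have changed anyway.

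The primary comparison, the secondary outcomes and the separate SEN analysis do not rely on this analysis. It is a worthwhile correction to the additional moderator analyses and does not threaten the trial's main conclusion.

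**What to change.** For school type, baseline bullying rate, rural or urban setting, proportion of students with SEN and concomitant activities, replace the within-arm analysis with treatment-by-covariate interactions in the full two-arm multilevel model. Fit them one at a time, report estimates with confidence intervals, and label them exploratory.

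Keep only intensity or adherence as a within-arm analysis. Use the classroom-level session data where possible, and report the result as a non-randomised association that school and classroom characteristics may confound.

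The cost is a change of analysis wording, with no new data. The interactions will be imprecise with 20 schools, and the text should say so.

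Suggested wording: *Modification of the intervention effect by school type, baseline bullying rate, rural or urban setting, proportion of students with SEN and concomitant activities will be explored by adding each treatment-by-covariate interaction separately to the multilevel model fitted to both arms. Within intervention schools, the association between intensity of delivery and outcome will be described and will not be interpreted as modification of the randomised effect.*

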### Trial Status

The feasibility study was conducted between March and May 2018. Selection, randomization, and recruitment of schools started in November 2018 and were completed in January 2019. Baseline assessment of the 20 participating schools (10 in each arm) started in late January 2019 and was completed in early February. In the intervention group, the 12-week intervention program was implemented from February through early May 2019. The post-intervention assessment was performed between late May 2019 and early June 2019. The one-year follow-up assessment will take place during the school year 2020-2021.

## Discussion

Bullying is a major preventable risk factor for mental and physical disorders (8, 9, 87). Increasing recognition of the long-term adverse effects of bullying victimization and perpetration has led to the development of several school-based interventions in the past 20 years (18, 88). These interventions have proven effective overall, even when applied for relatively short periods of time (<1 year) (17, 18, 88). Most of these interventions require extensive personnel effort and may incur very high immediate costs. Despite the evidence supporting the cost-effectiveness of these interventions (21), the feasibility and reach of these interventions could be improved by using less time-consuming methods, including web-based interventions. In the past decade, there has been an increase in digitally supported psychosocial interventions, which in some cases show efficacy comparable to face-to-face interventions (e.g., computerized cognitive-behavioral therapy for anxiety and depressive disorders in adolescents and young adults), although there is still insufficient information on the efficacy of some of these interventions and their cost-effectiveness (89). Digitally-enabled interventions could be especially useful in the field of primary prevention and mental health promotion (90), considering that universal preventive strategies need to target a very large number of subjects and should be as ecological as possible (87). Web-enabled interventions also facilitate standardization of interventions across settings and require less economic and time investment, thus facilitating dissemination to wider audiences, including low- or medium-income countries, where human and material resources are usually scarce, while there has been growing access to the Internet and smartphone technology in recent years (90, 91). Furthermore, the fact that children and adolescents are digital natives suggests that digitally delivered and supported interventions may have better acceptability, which is essential for the long-term sustainability of the intervention, beyond an experimental context.

An additional strength of the current intervention is the specific focus on children with special educational needs and other disabilities, including children on the autism spectrum. This study tries to address the lack of studies specifically assessing the efficacy of anti-bullying interventions in these populations, despite clearly higher rates of bullying and other forms of victimization and their negative effects on mental health (28, 34, 42). In this concern, the LINKlusive program adds to previous universal anti-bullying prevention programs by complementing personalized interventions for bullying cases with specific materials for teachers addressing bullying behavior that targets minority groups (e.g., young people with SEN, LGBT youth) and by focusing the student program on the promotion of respect for diversity.

The use of peer-reported measures of bullying behavior and the adaptation of content and assessment methods to youth with SEN are additional advantages of the current study design. Previous studies have shown poor correlations between self- and peer-reported measures of bullying (r ≈ 0.3) (62, 66, 92). The absence of anonymity in self-reports has been indicated as a possible reason for the low correspondence between self-reports and peer nominations (62), and some authors have suggested that some students may be uncomfortable labeling themselves as victims of bullying (93, 94). In children with SEN, especially in those with difficulties interpreting social situations, there may be additional limitations to recognizing and providing an accurate self-report of bullying situations (95), thus further supporting the use of peer-reported measures.

This study has several potential limitations. The most important of these would be the fact that the assessment method used in both treatment groups may also identify victims and guide some kind of intervention in the control group. However, since Sociescuela is widely used in the vast majority of publicly funded schools in the Madrid region, it would seem ethically inappropriate not to provide this information to the control group. The relatively low bullying victimization prevalence rates in our sample at baseline may also preclude detecting a significant effect of the active intervention due to a potential floor effect. Moreover, the need to postpone the follow-up assessment due to the COVID-19 pandemic and the organizational changes derived from social distancing and other preventive measures in schools (including smaller class size and greater supervision of unstructured periods) may affect our ability to detect a sustained effect of the intervention over time. The fact that students may change classrooms or even schools between school years may also influence results of the follow-up assessment. Furthermore, as we conducted our power calculation for the main outcome measure in the whole population, the sample size of the subgroup of students with SEN may be insufficiently powered to detect significant differences, even more so considering the heterogeneity of diagnoses within this group. Therefore, we plan to perform a sensitivity analysis in this subgroup and, based on this proof-of-concept, possibly conduct a larger study specifically testing the efficacy of the intervention in this subgroup in the future. The lack of allocation concealment may have some impact on the results, although, considering that the assessments are collected through the online platform and completed only by the students, we expect this effect to be limited. An additional source of potential bias lies in schools being offered participation after randomization and allocation to the intervention arms, which could have influenced their willingness to participate in the trial. However, this risk was mitigated by the fact that no experimental or control schools refused to participate. The fact that we are testing a multicomponent intervention means we are unable to infer which components may be more efficacious and what may work better for whom. If the LINKlusive program proves to be effective, further studies could assess the specific effect of its main components. Although we have included methods for assessing concomitant interventions in both groups and adherence to the intervention in the intervention group, it is difficult to systematically gather this information, which could affect the results to some extent. Finally, although self-reporting is considered a valid measure of psychopathology, especially in non-clinical contexts, we lack clinician-based measures of diagnosis or psychopathology. However, we do not expect this to significantly affect our main outcome measure. Furthermore, general and dimensional measures of psychopathology may be better suited to assessing short-term changes, and previous evidence suggests good convergent validity with clinician-based measures.

Despite these limitations, this study is the first one to test a web-enabled, user-friendly, anti-bullying intervention with a special focus on promoting diversity and addressing school bullying in mainstreamed young people with special educational needs. As bullying may be considered one of the most prevalent potentially modifiable risk factors for mental disorders (87), the efficacy of such an intervention may provide further support for implementing school-based anti-bullying programs globally, so as to improve life-long health and social outcomes worldwide.

## Ethics Statement

The studies involving human participants were reviewed and approved by the Deontology Commission of the School of Psychology, Universidad Complutense in Madrid, Spain. Written informed consent to participate in this study was provided by the participants' legal guardian/next of kin.
